*Tonic*	3. Emotional sharing will generally make sharers and supporters feel better, leading them to report positive mood changes. 4. Emotional sharing will generally help sharers to reappraise their feelings, leading them to report changes in emotional appraisals. 5. Compared to natural sharing, co-rumination may lead to equal or even more positive mood outcomes, possibly due to increased emotional closeness and perceived support. 6. Compared to natural sharing, co-rumination will be associated with smaller changes in emotional appraisals.
*Chronic*	7. Higher relationship quality and more constructive dyadic coping strategies will be associated with 1) stronger movement synchrony; 2) stronger cardiovascular synchrony; 3) stronger positive mood changes; 4) more emotional appraisal changes. 8. Higher relationship quality and constructive dyadic coping may buffer or attenuate potential differences between co-rumination and natural sharing in: (a) movement synchrony, (b) cardiovascular synchrony, (c) mood responses, and (d) emotional appraisal changes.

Moreover, we will conduct a series of exploratory analyses involving the secondary variables to further inform our understanding of interpersonal emotion regulation within close relationships. These exploratory analyses will probe the intricate connections between relational factors, individual characteristics, emotional sharing and physiological responses. In addition, in a second set of exploratory analysis we will be looking at synchrony in verbal communication: 1) linguistic synchrony; 2) vocal synchrony; 3) facial synchrony. These exploratory analyses are elaborated in Supplementary *1 in*
S1 File.

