### Co-rumination manipulation

We will experimentally manipulate the instructions of the emotional sharing task, following a validated procedure developed by Tudder et al (2023) [27]. For half of the sharing episodes, the supporter will receive instructions that promote co-rumination, which involves focusing on a topic, repeatedly discussing the issues, speculating about the antecedents and consequences of the issues, and exploring and unearthing negative emotions. For the other sharing episodes, the supporter will be instructed to respond in a natural way to the sharer. The order of the co-rumination versus natural response will be counterbalanced. Each member of the couple will be instructed once to engage in co-rumination and once to engage naturally with the sharer in all four conditions, the participants will receive digital instructions and physical cards to remind them of their role and the associated instructions.

Before the first sharing episode, participants will be taken by their experimenter to the emotional sharing space with the two armchairs (see Fig 1b), so that they can familiarize themselves with this space Then they will be taken back to their private space, where they will be informed about the first experience to address and be asked to “collect their thoughts” for two minutes. Following this, each participant will again be taken to the emotional sharing space. Participants will then engage in their first round of emotional sharing on the selected experience. After completing the first emotional sharing episode, the participants will go back to the private space and complete the post-dialogue survey about their sharing experience. After completing the first instruction, the instructions for natural sharing and co-rumination will be reversed, and after two rounds, the roles of the sharer and supporter will be switched, and vice versa.

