#### Tonic timescale.

***Mood change analysis:*** To assess changes in mood over time (Hypothesis 3), we will use linear mixed-effects models (LMMs), treating time (pre vs. post) and condition (co-rumination vs. natural sharing) as fixed effects, and including random intercepts for participants nested within dyads to account for the non-independence of dyadic partners and repeated measurements. This approach enables us to examine overall mood changes without splitting sharers and supporters into separate analyses.

For Hypothesis 5, we will examine whether mood following co-rumination differs from mood following natural sharing using the same LMM framework, focusing on post-sharing mood scores across conditions.

***Emotional appraisal analysis:*** To evaluate changes in emotional appraisals (Hypothesis 4), we will calculate change scores by subtracting the pre-sharing appraisal rating from the post-sharing appraisal rating for each emotional episode. These change scores will then be entered into linear mixed-effects models, with condition as a fixed effect and random intercepts for participants nested within dyads. This approach accounts for within-person and within-dyad dependence and avoids the use of separate t-tests for each condition. Hypothesis 6 will be tested by comparing appraisal change scores between the co-rumination and natural sharing conditions using the same dyadic LMM framework.

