#### Chronic timescale.

***Relationship quality and dyadic coping analysis:*** We will employ regression analysis to examine the associations between relationship quality and dyadic coping strategies and movement and cardiovascular synchrony (*Hypothesis 7.1 and 7.2*). Additionally, to analyse whether dyadic coping and relationship quality are associated with mood changes we will add these variables as fixed factors in the linear mixed models built for testing hypothesis 3 on mood change over time (*Hypothesis 7.3*). Linear regression analyses will also be used to assess whether relationship quality and dyadic coping are related to emotional appraisal change (*Hypothesis 7.4*).

To assess whether co-rumination versus natural sharing influences the relationship between higher relationship quality and more constructive dyadic coping and movement and cardiovascular synchrony moderated regression analyses will be used (Hypotheses 8.1 and 8.2). To analyse whether the associations between relationship quality and dyadic coping with mood change are associated with effects of co-rumination versus natural sharing we will extend the linear mixed models used for testing hypothesis 7.3. The full model will consist of a random intercept for participants, fixed factors of assessment time and condition, their interaction, and mood as the dependent variable (*Hypothesis 8.3*). Moderated linear regression analyses will be used to assess whether better relationship quality and dyadic coping are associated with weaker effects of the co-rumination condition versus natural sharing on emotional appraisal change (*Hypothesis 8.4*).

The hypotheses presented in Table 1 and the data analysis techniques utilized constitute the core elements of our research. Additionally, we have identified and measured a range of secondary variables that could potentially influence these associations. Our aim is to incorporate these variables as covariates in the analyses to enhance our understanding of the findings. For all statistical tests α ≤ 0.05 (two-tailed) will be applied. Given the wide range of statistical tests performed, there is a concern regarding multiple comparisons. Therefore, to reduce the likelihood of Type I errors, we will apply the Bonferroni correction to all previously mentioned test results.

***Exploratory analyses summary:*** In our study, we plan to conduct exploratory analyses to investigate interpersonal synchrony in verbal communication:

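### The Hypothesis 6 appraisal model has random intercepts only; these cancel from the condition contrast, so its standard error is too small if partners respond alike to the co-rumination instruction

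*Protocol article*

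**What the plan says.** The emotional appraisal paragraph under Tonic timescale defines the outcome as a change score, obtained by "subtracting the pre-sharing appraisal rating from the post-sharing appraisal rating for each emotional episode". These scores enter a linear mixed model "with condition as a fixed effect and random intercepts for participants nested within dyads". The article then states: "This approach accounts for within-person and within-dyad dependence". For the experimental contrast it adds: "Hypothesis 6 will be tested by comparing appraisal change scores between the co-rumination and natural sharing conditions using the same dyadic LMM framework".

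The section on the co-rumination manipulation fixes how condition varies: "Each member of the couple will be instructed once to engage in co-rumination and once to engage naturally with the sharer". Each sharer is therefore supported once under each instruction. A couple yields two appraisal change scores per sharer, four in all.

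Table 1, Hypothesis 8, proposes that couples differ in this contrast: "Higher relationship quality and constructive dyadic coping may buffer or attenuate potential differences between co-rumination and natural sharing", and its item (d) names appraisal change. The Chronic timescale section plans, as Hypothesis 8.4, to test whether "better relationship quality and dyadic coping are associated with weaker effects of the co-rumination condition versus natural sharing on emotional appraisal change".

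**The concern.** Random intercepts let partners resemble each other in how much their appraisals change overall. They do not let partners resemble each other in how much that change differs between the two instructions, and Hypothesis 6 tests only that difference. The model therefore takes the condition effect to be the same in every couple, apart from independent noise.

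Hypothesis 8(d) proposes that features of the relationship change the size of the effect. If that is so, the two partners in a couple will tend to deviate in the same direction, and the 300 differences are not 300 independent pieces of information. Hypothesis 6 is confirmatory and concerns the study's only experimental manipulation. Its interval could be too short and its p-value too small. The separate regression for Hypothesis 8.4 does not repair the Hypothesis 6 standard error. A random intercept per dialogue would not repair it either, if (as I read Hypothesis 4) each dialogue gives one appraisal change score, the sharer's.

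**Working it through.** **Inputs.** 150 dyads, two-sided alpha 0.05 and regression effect sizes 0.1 to 0.2 come from the article (Sample size determination; Chronic timescale). Two change scores per sharer, one per condition, follow from the manipulation section. The Design section speaks of manipulation between participants, but it also has each couple meet both conditions twice, and the Discussion calls the design within-subject. I use that reading. Rho is not in the article and is an assumption throughout.

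**The plan's own figures.** A two-sided t-test for d = 0.5 with 80% power needs 64 per group, 128 in total, as stated. Reading 0.1 and 0.2 as Cohen's f² in a regression with three predictors gives 114 and 59, also as stated. This sample size arithmetic is not in dispute. It supports reading the regression effect sizes as f², which is used below.

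**Algebra.** For couple i, sharer j and condition c = ±1/2, the stated model is

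y = μ + βc + u_i + v_ij + e.

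The sharer's condition difference is D_ij = β + e₁ − e₂. Both u_i (dyad) and v_ij (participant) drop out. The model therefore gives

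SE(mean D) = SD(D)/√(2N) = SD(D)/√300 = 0.0577 SD(D), whatever rho is.

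Now let the condition effect vary by couple, adding b_i·c with variance τ². The two partners' differences then share b_i and correlate at rho = τ²/(τ² + 2σ²), where σ² is the residual variance. The true standard error is

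SE(mean D) = SD(D)·√(1 + rho)/√(2N).

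The actual type I error at nominal 0.05 is 2[1 − Φ(1.96/√(1 + rho))].

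**A scale for rho from the plan's effect sizes.** R² = f²/(1 + f²), so 0.1/1.1 = 0.091 and 0.2/1.2 = 0.167. If moderators wholly shared by the couple explained that share of the variance of D, and nothing else were shared, rho would equal R². The last two rows of the table are illustration only.

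| rho | √(1+rho) | true SE, in SD(D) | planned interval too narrow by | type I error |
|---|---|---|---|---|
| 0 | 1.000 | 0.0577 | 0% | 0.050 |
| 0.091 | 1.044 | 0.0603 | 4.3% | 0.061 |
| 0.167 | 1.080 | 0.0624 | 7.4% | 0.070 |
| 0.3 | 1.140 | 0.0658 | 12.3% | 0.086 |
| 0.5 | 1.225 | 0.0707 | 18.4% | 0.110 |

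**Simulation check** (150 couples, no true effect, 20,000 replicates). Treating the 300 differences as independent rejected in 4.9%, 6.2%, 7.0%, 8.4% and 10.7% of runs for the five rows. Testing couple means rejected in 4.8% to 5.2%. Mixed models fitted to 12 data sets at rho = 0.3 gave a mean SE of 0.0574 with intercepts only and 0.0651 with a dyad-level condition effect.

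**Bonferroni threshold.** The article applies the correction but gives no divisor. Assuming 8, one per hypothesis in Table 1, the threshold is 0.00625. The actual error is then 0.0088 at rho 0.091 (0.0088/0.00625 = 1.4 times nominal) and 0.0114 at rho 0.167 (1.8 times). At 0.05 the corresponding ratios are 1.2 and 1.4.

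**The case against.** - **Rho is unknown and may be small.** This stands. The article gives no value. Hypothesis 8 is worded as a possibility, so differing responses are under test and not assumed. The Introduction also expects little appraisal change in strong couples, and little in weaker ones under co-rumination.
- **The moderators are not couple-level scores.** Each partner completes the questionnaires, and the Abstract speaks of individual differences. Moderation by a person's own score correlates the partners' responses only through what the two scores share. Assuming partner-score correlations of 0.3 to 0.7 (not in the article), rho runs from 0.3 × 0.091 = 0.03 to 0.7 × 0.167 = 0.12, and type I error from 5.3% to 6.4%. This stands as a reason to expect the lower end, although other shared sources of variation are possible.
- **The sentence on dependence is correct for Hypothesis 4.** This stands. It follows the Hypothesis 4 model and is right for average levels. A reader might infer that it is simply false; it is incomplete for the contrast that comes next.
- **Bonferroni keeps the absolute error low.** This stands. Even at rho 0.5 with a divisor of 8 the error is 0.0256, below 5%. The correction still does not mend a wrong standard error, and the relative excess grows as the threshold tightens.
- **A condensed article may leave random slopes to a fuller plan.** This has limited force. The article names the random terms for this model and declares them sufficient, so the point concerns what is written.

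**Conclusion.** The point holds in conditional form. The stated model is valid for Hypothesis 6 only if the couple-by-condition variance is zero, which sits badly with Hypotheses 8(d) and 8.4. If that variance is positive, the standard error is short by √(1 + rho), and by no more than √2 in this design.

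On the plan's own effect sizes, with moderation fully shared within couples, the type I error is about 6% to 7% instead of 5%. It is lower with partial sharing. A reader might infer that the Hypothesis 6 intervals are certainly too narrow, or that the error reaches 9% to 11%. The documents support neither: the first needs rho > 0, which is proposed but not established, and the second needs rho of 0.3 to 0.5, for which the article gives no basis. Severity is minor to moderate.

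**What to change.** For Hypothesis 6, add a random effect of condition by dyad to the appraisal change model and keep the dyad and participant intercepts. A close alternative is to average the two partners' co-rumination minus natural differences and test the 150 couple means against zero; this also allows a negative correlation between partners. Qualify the sentence on dependence: the random intercepts cover partners' average change, and the condition-by-dyad term covers their response to the instruction.

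The change needs no new data. The interval widens by about √(1 + rho): 4% to 8% for rho 0.09 to 0.17, and about 22% at rho 0.5. Because an estimated variance cannot fall below zero, the random-effect version also widens it slightly when couples respond alike, by about 1.6% on average in a simulation of 150 couples with rho = 0.

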#### Chronic timescale.

***Relationship quality and dyadic coping analysis:*** We will employ regression analysis to examine the associations between relationship quality and dyadic coping strategies and movement and cardiovascular synchrony (*Hypothesis 7.1 and 7.2*). Additionally, to analyse whether dyadic coping and relationship quality are associated with mood changes we will add these variables as fixed factors in the linear mixed models built for testing hypothesis 3 on mood change over time (*Hypothesis 7.3*). Linear regression analyses will also be used to assess whether relationship quality and dyadic coping are related to emotional appraisal change (*Hypothesis 7.4*).

To assess whether co-rumination versus natural sharing influences the relationship between higher relationship quality and more constructive dyadic coping and movement and cardiovascular synchrony moderated regression analyses will be used (Hypotheses 8.1 and 8.2). To analyse whether the associations between relationship quality and dyadic coping with mood change are associated with effects of co-rumination versus natural sharing we will extend the linear mixed models used for testing hypothesis 7.3. The full model will consist of a random intercept for participants, fixed factors of assessment time and condition, their interaction, and mood as the dependent variable (*Hypothesis 8.3*). Moderated linear regression analyses will be used to assess whether better relationship quality and dyadic coping are associated with weaker effects of the co-rumination condition versus natural sharing on emotional appraisal change (*Hypothesis 8.4*).

The hypotheses presented in Table 1 and the data analysis techniques utilized constitute the core elements of our research. Additionally, we have identified and measured a range of secondary variables that could potentially influence these associations. Our aim is to incorporate these variables as covariates in the analyses to enhance our understanding of the findings. For all statistical tests α ≤ 0.05 (two-tailed) will be applied. Given the wide range of statistical tests performed, there is a concern regarding multiple comparisons. Therefore, to reduce the likelihood of Type I errors, we will apply the Bonferroni correction to all previously mentioned test results.

***Exploratory analyses summary:*** In our study, we plan to conduct exploratory analyses to investigate interpersonal synchrony in verbal communication:

**Verbal expressions and word use:** We will analyze the frequency and context of specific words used during emotional sharing to see how they correlate with mood and personality changes, and relationship quality.**Vocal arousal coding:** Vocal characteristics such as arousal and pitch variations will be examined to understand their correlations with emotional states and personality traits during interactions.**Facial expression coding:** We will employ facial expression coding to study the emotional responses visible during the sharing tasks, assessing their relationship with mood change and personality traits.

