## Methods and statistical analysis

### Design

This study has a mixed factorial-experimental nested design. In total, each couple engages four times in the emotional sharing task, twice in the co-rumination and twice in the natural sharing condition. Each participant will twice share a distressing experience and will twice act as supporter. Both aspects will be experimentally manipulated between participants. Measures of mood and appraisal will be nested within participants, while movement and cardiovascular synchrony will be nested within dyads. The chronic variables (i.e., dyadic coping and relationship variables) will be used correlational.

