Specifically, in each 8-minute dialogue, the motion energies of both participants will be cross-correlated in non-overlapping window segments of 30 seconds. The choice of a 30-second window size (750 frames) is to account for the shorter turn-taking latencies in question-centered discussions, consistent with previous work [30]. Windowed cross lagged cross-correlation of up to 5 seconds of positive and negative time lags will be computed with a step size of 0.1 seconds, achieved by progressively shifting one time series relative to the other [9]. The resulting matrix of cross-correlations will then be transformed using Fisher’s r-to-Z transformation, and their absolute values will be aggregated over the entire 8-minute interval of the dialogue, resulting in a shared global value of nonverbal synchrony for every sharing episode [9].

To ascertain whether the synchrony detected via MEA exceeded what might occur by chance (i.e., pseudosynchrony), we will engage a specific RMEA function designed for generating pseudointeractions through automated surrogate algorithms. This function shuffles the days in the data and calculates all possible motion energy interactions between couples in the dataset. Subsequently, it dissociates the original pairings, followed by the extraction of a predefined amount of unique MEA datasets, each selected just once to avoid duplication.

To test Hypothesis 1, we will examine whether relationship partners show greater synchrony than pseudo-dyads during the emotional sharing tasks. Following recommendations by Helm et al. (2018) [31] and DiGiovanni et al. (2024) [18], we will compute windowed cross-correlations to generate time series of movement synchrony. We will then apply multilevel modeling (MLM) using the *lme4* package in R to compare synchrony scores between real dyads and matched pseudo-dyads, accounting for the nested structure of time windows within dyads. To test Hypothesis 2, we will examine whether co-rumination leads to greater synchrony than natural sharing. Movement synchrony data will be modeled using multilevel models with time windows (Level 1) nested within participants (Level 2) and dyads (Level 3). Experimental condition (co-rumination vs. natural sharing) will be entered as a fixed effect predictor, and dyad ID and participant ID will be modeled as random effects. This approach accounts for both the repeated nature of the synchrony time series and the interdependence between partners in a dyad.

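### Six chronic-timescale tests (H7.1, H7.2, H7.4, H8.1, H8.2, H8.4) are assigned plain regression with no allowance for clustering, although the same outcomes are treated as nested and given mixed models elsewhere; the conflict is firmest for H7.4 and H8.4

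*Protocol article*

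**What the plan says.** **Data structure.** Under Design, the protocol article states that "each couple engages four times in the emotional sharing task, twice in the co-rumination and twice in the natural sharing condition". It adds that "movement and cardiovascular synchrony will be nested within dyads" and "Measures of mood and appraisal will be nested within participants". Movement synchrony is reduced to one number per dialogue, "resulting in a shared global value of nonverbal synchrony for every sharing episode" (Phasic timescale). Appraisal change is computed separately for each emotional episode (Tonic timescale).

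**Models for H1–H6.** Synchrony is compared by multilevel models (H1, H2). Appraisal change is analysed by mixed models with participants nested in dyads (H4, H6), and the reason is given: "This approach accounts for within-person and within-dyad dependence".

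**Models for H7 and H8 (Chronic timescale).**
- H7.1, H7.2: "We will employ regression analysis to examine the associations between relationship quality and dyadic coping strategies and movement and cardiovascular synchrony".
- H7.3: the linear mixed model from H3, extended.
- H7.4: "Linear regression analyses will also be used to assess whether relationship quality and dyadic coping are related to emotional appraisal change".
- H8.1, H8.2: moderated regression.
- H8.3: an extended linear mixed model.
- H8.4: "Moderated linear regression analyses will be used to assess whether better relationship quality and dyadic coping are associated with weaker effects".

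For the six regression-based sub-hypotheses, the text states no random effect, no cluster-robust standard error and no reduction to one row per couple.

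**The concern.** The same outcome is handled in two ways. Appraisal change gets a dyadic mixed model for H4 and H6 and a linear regression for H7.4 and H8.4. Synchrony gets multilevel models for H1 and H2 and regression for H7.1, H7.2, H8.1 and H8.2. Within the chronic section, regression stands beside linear mixed models for H7.3 and H8.3, so it does not read as shorthand for a mixed model.

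If the episode rows go into a regression as though independent, the error depends on the term:

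- **H7** concerns predictors that belong to the couple or the person. Correlated rows are counted as separate information, the standard error is too small, and false positives rise.
- **H8** concerns condition × moderator, and condition varies within the couple. Stable differences between couples stay in the error term, the standard error is too large, and power is lost.

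The article's introduction expects relationship quality and coping to matter much more than the manipulation does, so these tests are central to the study.

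**Working it through.** **Inputs from the protocol article:** 150 dyads; four episodes per dyad, two per condition; each partner shares twice, once under each instruction; α = 0.05 two-tailed; Bonferroni correction. **Not given, so assumed:** the ICC ρ and its split between dyad and person.

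**1. The plan's own regression figure.** The omnibus F test with noncentrality f²·N, 80% power, α = 0.05 and three predictors gives N = 59 at f² = 0.2 and N = 114 at f² = 0.1. This matches the stated 59–114 dyads. The three predictors and the f² scale are inferred because they reproduce the figures. The calculation takes one independent row per dyad, whereas the outcomes come as four rows per dyad, 150 × 4 = 600.

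**2. H7.1, H7.2 with episode rows stacked.** For a couple-level predictor that is constant over four rows, true/naive variance = 1 + 3ρ, and type I error = 2·[1 − Φ(1.96/√(1 + 3ρ))].

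| ρ | 1 + 3ρ | 600/(1 + 3ρ) | Type I error |
|---|---|---|---|
| 0.2 | 1.6 | 375 | 12.1% |
| 0.3 | 1.9 | 316 | 15.5% |
| 0.5 | 2.5 | 240 | 21.5% |

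A simulation of 150 dyads × 4 episodes (3,000 runs) gave 15.1% at ρ = 0.3 and 21.8% at ρ = 0.5.

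**3. H7.4 with episode rows stacked.** The predictor is each sharer's own score, so it differs between partners and 1 + 3ρ does not apply. Assume a partner correlation of 0.5 in the predictor, a dyad variance share d and a person share p. Each row has one other row from the same person (residual correlation d + p) and two from the partner (residual correlation d, predictor correlation 0.5). The factor is 1 + (d + p) + 2·0.5·d = 1 + 2d + p.

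| d, p | Factor | Type I error, formula | Type I error, 3,000 simulations |
|---|---|---|---|
| 0.1, 0.1 | 1.3 | 8.6% | 8.4% |
| 0.1, 0.3 | 1.5 | 11.0% | 11.3% |
| 0.2, 0.3 | 1.7 | 13.3% | 12.0% |

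Averaging to one row per participant does not remove the dependence. The partner correlation of the averages is d/[d + p + (1 − d − p)/2], that is 0.167, 0.143 and 0.267. The factor 1 + 0.5 × that correlation is 1.083, 1.071 and 1.133, and type I error is about 6–7%.

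**4. H8 with episode rows stacked.** For a balanced within-couple term, true/naive variance ≈ 1 − ρ, so the naive standard error is too large by the ratio k = 1/√(1 − ρ). A test that would have 80% power with the correct standard error has noncentrality 1.96 + 0.84 = 2.80. Its power with the overstated one is Φ(2.80 − 1.96k).

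- ρ = 0.3: k = 1.20, Φ(0.46) ≈ 68%.
- ρ = 0.5: k = 1.41, Φ(0.03) ≈ 51%.

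Simulated power for an assumed interaction of 0.2 SD was 72% with stacked regression against 83% with a within-couple analysis at ρ = 0.3, and 75% against 92% at ρ = 0.5. For H8.4, ρ is the same-person share d + p.

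**5. Bonferroni.** Count, as an assumption, 24 confirmatory tests: eight for H1–H6, plus 2 predictors × 4 outcomes × 2 hypotheses = 16. The threshold is 0.05/24 = 0.21%, z = 3.078. For H7.1/H7.2 the true per-test error is 2·[1 − Φ(3.078/√(1 + 3ρ))] = 1.5%, 2.6% and 5.2% at ρ = 0.2, 0.3 and 0.5. The correction lowers the threshold but leaves the wrong standard error in place.

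**The case against.** **Regression need not mean stacked rows.** For H7.1 and H7.2 the article does not say ordinary least squares on episodes. Its sample-size section counts dyads for regression, which fits one averaged synchrony value per dyad, and the standard errors would then be valid. This stands as a possibility. No passage states the averaging, and the only synchrony summary described is per episode.

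**H8 can be done by regression.** A reader might infer that, because condition varies within the couple, a moderated regression has to treat repeated rows as independent. That does not follow. Regressing each couple's co-rumination-minus-natural difference on the moderator tests the same interaction with one row per couple. For H8.1 and H8.2 this would be valid, but the article does not state it.

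**The largest figures do not cover every H7 test.** A reader might apply 12–22% to all of H7. Those figures need a predictor that is constant over all four rows. H7.4, where linear regression is named outright, shows the smaller inflation in step 3.

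**The H8 error is conservative.** It costs power and adds no false positives. That is correct, but a test that can fall from 80% to between 51% and 68% power is still a poor choice when the remedy is this cheap.

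**A condensed article leaves detail to a fuller plan.** Row layout could be such detail. The model class is not: the article assigns one to each hypothesis, and the class assigned here conflicts with its own account of the data.

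**Conclusion.** The chronic section conflicts with the Design, phasic and tonic sections and should be corrected before analysis. The conflict is firmest for H7.4 and H8.4: the same change scores are given a dyadic mixed model two paragraphs earlier, and partners stay correlated even with one row per participant. For H7.1, H7.2, H8.1 and H8.2 the defect is conditional. The standard errors are wrong if episode rows are treated as independent, and the article states nothing that would prevent this. The documents do not support the stronger claim that all six are bound to be invalid.

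Under stacked rows, the direction holds for any positive ICC: H7 anti-conservative, H8 conservative. The size rests on assumptions. Type I error is about 12/16/22% for H7.1 and H7.2 at ICC 0.2/0.3/0.5. For H7.4 it is about 8–12% by simulation and 9–13% by formula. Power for H8 falls from 80% to about 68% or 51% at ICC 0.3 or 0.5.

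**What to change.** Replace the six regressions in the chronic section with mixed models.

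- **Appraisal change (H7.4, H8.4):** the model already given for H4 and H6, with random intercepts for participants nested in dyads. Add the relationship quality and dyadic coping scores and, for H8.4, their interactions with condition.
- **Synchrony (H7.1, H7.2, H8.1, H8.2):** one row per couple-episode, a dyad random intercept and couple-level relationship quality and coping as predictors. Add their interactions with condition for H8.1 and H8.2. State how the two partners' scores form the couple-level value. The H2 movement model cannot be carried over unchanged, because it nests time windows within participants within dyads.
- **All H8 terms:** add a random condition slope by dyad where it can be estimated, or use dyad-clustered standard errors. If the condition effect varies between couples, a random intercept alone can understate the interaction's standard error.

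If averaged synchrony or within-couple differences were the intention, stating so would settle H7.1/H7.2 and H8.1/H8.2 respectively; H7.4 and H8.4 would still need aligning with the tonic section.

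Cost: a change of wording and a few lines of lme4 code. No new data are needed.
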